# Parathyroid autotransplantation at a novel site for better evaluation of the grafted gland function: study protocol for a prospective, randomized controlled trial

**DOI:** 10.1186/s13063-019-3195-9

**Published:** 2019-01-31

**Keywords:** Parathyroid autotransplantation, Novel site, Assessing method, Parathyroid hormone

## Abstract

**Background:**

Hypoparathyroidism is one of the most common complications encountered in thyroidectomy. In addition to parathyroid in-situ preservation, parathyroid autotransplantation (PA) is another important remedial method for patients whose parathyroid glands have been removed. However, an accurate evaluation method for the function of a transplanted parathyroid is lacking. Our preliminary study indicated that patients with PA at novel sites near antecubital veins had higher serum concentrations of parathyroid hormone (PTH). Therefore, the main hypothesis is that a grafted site closer to the cephalic vein is more useful for better evaluation of transplanted parathyroid function. This study aims to confirm the more efficient and accurate evaluation system through a prospective, randomized controlled trial.

**Methods:**

In total, 280 patients will be enrolled in this study and randomly divided into two groups: 140 patients with transplanted parathyroid glands in the traditional sites (group A) and the other 140 transplanted in the novel sites (group B), close to the antecubital veins. The serum concentration of PTH and calcium ion from both forearms will be measured and monitored regularly for 12 months. The primary outcome of this trial will be the survival of grafted glands, defined as the ratio of PTH between the grafted vs. the non-grafted forearms being no less than 1.5. The secondary outcome is hypoparathyroidism, defined as the PTH level from the non-grafted forearms being less than 15 pg/ml (normal range 15–65 pg/ml).

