**Discussion:**

Our results from this study should provide a more accurate method to evaluate the function of transplanted parathyroid glands by comparing PTH concentrations in both the grafted and non-grafted forearms following PA at novel sites. A better PTH measurement is helpful not only for the management of postoperative patients, but also for further identification of factors affecting PA success.

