In the previous study of PA in thyroidectomy, the grafted site in the forearm strategy was applied to several patients who had been examined and found to have a higher concentration of serum PTH from the closer-to-antecubital-vein graft sites than the more distant ones. To promote the accuracy of this PTH-gradient method to evaluate PA success for thyroidectomy patients after autotransplantation with normal parathyroid glands, we hypothesized that PA at a novel site closer to the antecubital veins could result in a higher concentration of serum PTH and a more accurate ratio of PTH from the grafted forearm relative to the non-grafted one. Vice versa, the null hypothesis was that there was no significant difference of either serum concentration or ratio of PTH from both forearms. This prospective, randomized controlled trial aims to establish a modified PTH-gradient method by PA at the novel sites to promote the accuracy of transplanted parathyroid gland evaluation. Our results should contribute to a more accurate evaluation of transplanted parathyroid function in PA patients, and facilitate further investigation of potential factors affecting the survival of transplanted parathyroid glands.

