## Methods

### Study design

This is a prospective, randomized controlled trial to apply PA at the novel sites and to assess the survival rate of transplanted parathyroid glands in thyroidectomy patients. A 1:1 block randomization will be performed at the same clinical center and operations will be carried out by the same experienced surgeon in Tongji Hospital (Wuhan, China). The study has been approved by the Ethics Committee of Tongji Hospital, Tongji Medical College, Huazhong University of Technology Institutional Review Board with approval given on 25 June 2015 (reference number: TJ-C2015602) (Additional file 1).

In this single-center study, hospitalized patients with primary thyroidectomy in Tongji Hospital will be enrolled. Stochastic indicators were used to generate the random allocation sequence of the patients. Sequentially numbered containers were employed to implement the random allocation sequence and to conceal the sequence until interventions are assigned for implementation. Analysts in our study generated the random allocation sequence while care providers numbered the qualified participants. The surgeon assigned participants to interventions based on the condition of their parathyroid glands during thyroidectomy. All subjects, researchers in the laboratory and data analysts will be blind to the group classification.

Primary endpoint: the ratio of the serum PTH level from the grafted vs. the non-grafted forearm level is no less than 1.5 and the percentages of the 1.5 ratio in the experimental group are obviously higher than those in the control group. Since successful PA was defined as the ratio of the PTH level from the grafted to the non-grafted forearms as not less than 1.5, we set the primary endpoint in line with expert opinion, and the percentages of no less than the 1.5 ratio in the experimental group are obviously higher than those in the control group. 

Secondary endpoints: serum PTH less than 15 pg/ml, and lasting for more than 6 months, as well as a low serum calcium level requiring oral supplements to be taken. Duration of hospital stay will be documented according to hospital charts. During the 1-month to 12-month follow-ups after surgery, patients will be interviewed to assess for postoperative hypocalcemia.

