### Outcome measures

Basal concentrations of PTH from both arms and the concentration of serum calcium will be obtained before and after surgery. Postoperative evaluation of symptoms and signs of hypocalcemia will be recorded as well as oral supplements with calcium and calcitriol. Two researchers will be assigned to record the examination results of participants, and to take blood samples.

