## Discussion

This is a prospective, randomized controlled trial comparing the evaluation efficiency of the novel site method and the traditional site method of PA in thyroidectomy. The purpose is to investigate whether the novel site close to the cephalic vein could be used to evaluate the function of transplanted parathyroid glands more accurately. Hypoparathyroidism is one of the most common complications in surgeries for thyroid carcinoma [20] because the parathyroid glands are sometimes prone to inadvertent damage, becoming devascularized, or being removed [21]. It has been reported that permanent hypoparathyroidism could be prevented by PA [22]. However, there exists controversy regarding PA efficiency after thyroidectomy [23, 24]. Therefore, it is necessary to establish a more efficient evaluation system for the transplanted parathyroid function.

The novel site for PA might provide a more accurate method to assess PA survival through biochemical measurement of the PTH ratio from the grafted and non-grafted forearms. To test this theory, the current prospective, randomized controlled trial was initiated. This new evaluating system could improve the measurement of the PTH ratio between the grafted and non-grafted forearm and will be convenient for the further study of PA regulation.

The strengths of the study include the prospective, randomized controlled trial design of the novel PA sites combining with the application of the PTH-ratio assessing system. In addition, a digitalized patient chart system ensures easy access, facilitating follow-up.

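### The primary outcome is labelled graft survival and is to be read as better accuracy, but a PTH ratio of at least 1.5 cannot separate survival from detectability when graft site is the intervention

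*Protocol article*

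**What the plan says.** The protocol article reads one proportion in two ways.

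*As graft survival.* The abstract (Methods) says "The primary outcome of this trial will be the survival of grafted glands, defined as the ratio of PTH" between the two forearms being at least 1.5. Study design says the trial is "to assess the survival rate of transplanted parathyroid glands in thyroidectomy patients". Data management and statistical analysis treats the ratio as the sign that a graft has survived and assigns it a chi-square test. Data monitoring describes an interim look at differences in survival between methods.

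*As accuracy of evaluation.* The aim in the Background is "to establish a modified PTH-gradient method by PA at the novel sites to promote the accuracy of transplanted parathyroid gland evaluation". The abstract's Discussion says "Our results from this study should provide a more accurate method to evaluate the function of transplanted parathyroid glands". The main Discussion gives the purpose as finding out whether the novel site could be used to "evaluate the function of transplanted parathyroid glands more accurately".

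The criterion that serves both readings is, in Study design, that "the percentages of the 1.5 ratio in the experimental group are obviously higher than those in the control group".

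The mechanism is in the Background: "we hypothesized that PA at a novel site closer to the antecubital veins could result in a higher concentration of serum PTH". Under PA protocol, follow-up blood comes from the vein near the graft and from the opposite forearm.

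**The concern.** Graft site is the randomised factor, and it is also part of the measurement. Placing the graft nearer the sampled vein may raise PTH in that sample even if the graft is no more likely to live. Randomisation balances the patients, but it cannot separate the effect of site on viability from its effect on detectability, because both follow from the same allocation.

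Separating them would need an independent determination of whether each graft works. None appears among the endpoints in Study design, the postoperative variables or the outcome measures. The Background itself says that the usual combination of symptoms and serum PTH cannot tell transplanted glands from remaining ones.

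At stake is what a positive trial would mean. A sampling effect could be reported as better survival, or a survival effect as a better test. The Cox model for factors affecting graft survival, the subgroup comparisons and the interim analysis rest on the same outcome and inherit the ambiguity.

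**Working it through.** **Inputs from the document (Sample size calculations):** 45% traditional, 65% novel, two-sided α 0.05, power 0.90, 128 per arm, 280 in total (140 per arm).

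**The plan's own figure.** With pooled variance, no continuity correction and mean proportion 0.55:

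- n = [1.960·√(2·0.55·0.45) + 1.2816·√(0.45·0.55 + 0.65·0.35)]² / 0.20²
- = [1.379 + 0.883]² / 0.04 = 127.9, rounded up to 128.

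This reproduces the stated 128. Power is 0.900 at 128 per arm and 0.924 at 140. The sample size is not at fault.

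**What the observed proportion contains.** Let S be true graft survival, and let Se and Sp be the sensitivity and specificity of the ratio rule at a given site. Then

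P(ratio ≥1.5) = S·Se + (1 − S)·(1 − Sp).

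Each arm supplies one proportion that depends on three unknowns. The trial therefore has two observed proportions for six unknowns.

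**Three explanations of 45% versus 65%.** The values of S, Se and Sp are assumptions; the document gives none. Sp = 1 throughout, so P = S·Se and overall accuracy = S·Se + (1 − S).

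| Case | Traditional: S × Se | Novel: S × Se | Observed | Accuracy |
|---|---|---|---|---|
| 1. Survival differs, perfect test | 0.45 × 1 | 0.65 × 1 | 45% vs 65% | 1.00 vs 1.00 |
| 2. Equal survival, better detection | 0.90 × 0.500 | 0.90 × 0.722 | 45% vs 65% | 0.55 vs 0.75 |
| 3. Worse survival, much better detection | 0.80 × 0.5625 | 0.70 × 0.929 | 45% vs 65% | 0.65 vs 0.95 |

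The chi-square test sees only the observed proportions, so its power is 0.924 at 140 per arm in all three cases. A larger sample makes the 20-point difference more precise without showing which case produced it.

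Case 1 is a survival gain with no gain in accuracy. Case 2 is the reverse. In case 3 the trial would report better survival although fewer grafts lived at the novel site.

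**The case against.** The best defence is that the trial is plainly about measurement. The title, aim and hypothesis concern evaluation, and Limitations says the system serves only to evaluate survival and leaves factors that improve it to later work. Both arms share one surgeon, one way of preparing the gland and subcutaneous injection. If true survival is equal and a dead graft creates no gradient at either site, a higher positive rate does mean higher sensitivity at unchanged specificity, and so better accuracy.

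That reasoning is valid and rules out saying that the result could never support an accuracy claim. But it rests on two assumptions that the article does not state, and the outcome label, design statement, analysis section and interim analysis all speak of survival.

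A reader might also infer that false positives at the novel site could produce the whole difference. With survival 45% and sensitivity 1 in both arms, that would need novel-site specificity of about 64% (0.45 + 0.55 × 0.364 = 0.65) against 100% at the traditional site. The documents do not support this. A dead graft secretes no PTH wherever it lies, so measurement noise should affect both arms alike. If noise alone were responsible, with a lognormal ratio of SD √(2·ln(1 + CV²)), a 36.4% false-positive rate would need a CV of about 98% in one arm and almost none in the other. No mechanism for that is given.

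**Conclusion.** The point holds as one of outcome definition and interpretation. The sample size and the chi-square test are unaffected. The planned 20-point difference can be read as a difference in the rate of a detectable PTH gradient. It does not by itself show better survival. It shows better sensitivity or accuracy only if true survival and specificity are equal at the two sites. The cases rest on assumed values of survival and sensitivity; that one proportion per arm cannot identify them does not depend on the values chosen.

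A reader might infer that the pre-operative two-forearm PTH could settle the matter by showing no excess of ratios ≥1.5 in the novel-site group. It cannot. Those samples precede grafting, and the allocation envelope is opened at the intervention, so the groups can differ only by chance. Passing such a check would also permit an accuracy claim in case 1, where accuracy is identical.

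**What to change.** 1. Rename the primary outcome *PTH-gradient positivity (ratio ≥1.5)* wherever it is now called survival, and limit the primary conclusion to detection rate.
2. State that reading the result as better sensitivity or accuracy assumes equal true survival and equal specificity at both sites. Do not claim better survival from it.
3. Add a between-group comparison of log(grafted/non-grafted PTH), adjusted for the pre-operative log ratio. Outcome measures already provides for this: "Basal concentrations of PTH from both arms and the concentration of serum calcium will be obtained before and after surgery". The Preoperative variables list mentions only serum PTH, so confirm that both forearms are sampled before surgery. This analysis shows the size of the gradient and allows for any prior side difference; it does not separate survival from detection either.
4. Report the pre-operative share with ratio ≥1.5, pooled over groups, only as a bound on positivity due to noise and not as a condition for claiming accuracy.
5. Report continuous non-grafted-forearm PTH by randomised group as supportive evidence on whether graft function differs by site. It already underlies the hypoparathyroidism outcome. Note that remaining glands contribute to it, so any difference is diluted and it is no patient-level reference.

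The cost is a narrower headline claim and slightly more analysis of measurements already planned. The sample size and visits do not change.

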**Discussion:**

Our results from this study should provide a more accurate method to evaluate the function of transplanted parathyroid glands by comparing PTH concentrations in both the grafted and non-grafted forearms following PA at novel sites. A better PTH measurement is helpful not only for the management of postoperative patients, but also for further identification of factors affecting PA success.

**Trial registration:**

ClinicalTrials.gov, ID: NCT02906748. Registered on 16 March 2016.

**Electronic supplementary material:**

The online version of this article (10.1186/s13063-019-3195-9) contains supplementary material, which is available to authorized users.

## Background

Parathyroid autotransplantation (PA) is an important technique for dealing with parathyroid glands removed in thyroidectomy and other neck surgeries [1, 2]. Unintentional parathyroidectomy is a major cause of postoperative hypoparathyroidism in total thyroidectomy with or without lymph node dissection [3, 4]. The incidence of unintentional parathyroidectomy during thyroidectomy has been shown to be 9–19% [5]. It has been reported that the number of remaining parathyroid glands in situ is a predictive variable for the rate of permanent hypoparathyroidism [6]. Although most parathyroid glands were preserved in situ in this study, permanent hypoparathyroidism was still observed frequently [6]. The incidence of permanent hypoparathyroidism could be up to 14.3% [7, 8] after thyroidectomy. PA has been reported to reduce the rate of permanent hypoparathyroidism [8, 9].

Our previous studies, recruiting 218 patients with thyroidectomy [10], indicated that approximately 17.5% of patients needed the partial tissue of one parathyroid gland for autotransplantation, and that 6.6% needed one or more integral parathyroid gland(s). However, there was no widely accepted, accurate method to evaluate the transplanted parathyroid glands. The currently popular method is to combine clinical symptoms and parathyroid hormone (PTH) serum concentration. However, this method cannot distinguish between the function of the remaining and transplanted parathyroid glands.

The PTH-gradient method, which compares serum PTH concentrations between the grafted and the non-grafted forearms, was originally applied to examine the function of transplanted parathyroid glands in patients with hyperparathyroidism [11]. A ratio of PTH from the grafted to non-grafted forearms of no less than 1.5 was considered to confirm successful PA [12]. It was mostly applied to monitor PTH in hyperparathyroidism patients with parathyroidectomy after PA [13, 14]. Rothmund et al. reported that the survival rate of PA with hyperparathyroidism was 31% (20 patients) [15], and Anamaterou et al. suggested that the survival rate was 45% in 19 patients using the ischemic-blockage Casanova test [16]. There are few reports regarding randomized controlled trials to evaluate the function of transplanted parathyroid glands using this PTH-gradient method.

In the previous study of PA in thyroidectomy, the grafted site in the forearm strategy was applied to several patients who had been examined and found to have a higher concentration of serum PTH from the closer-to-antecubital-vein graft sites than the more distant ones. To promote the accuracy of this PTH-gradient method to evaluate PA success for thyroidectomy patients after autotransplantation with normal parathyroid glands, we hypothesized that PA at a novel site closer to the antecubital veins could result in a higher concentration of serum PTH and a more accurate ratio of PTH from the grafted forearm relative to the non-grafted one. Vice versa, the null hypothesis was that there was no significant difference of either serum concentration or ratio of PTH from both forearms. This prospective, randomized controlled trial aims to establish a modified PTH-gradient method by PA at the novel sites to promote the accuracy of transplanted parathyroid gland evaluation. Our results should contribute to a more accurate evaluation of transplanted parathyroid function in PA patients, and facilitate further investigation of potential factors affecting the survival of transplanted parathyroid glands.

## Methods

### Study design

This is a prospective, randomized controlled trial to apply PA at the novel sites and to assess the survival rate of transplanted parathyroid glands in thyroidectomy patients. A 1:1 block randomization will be performed at the same clinical center and operations will be carried out by the same experienced surgeon in Tongji Hospital (Wuhan, China). The study has been approved by the Ethics Committee of Tongji Hospital, Tongji Medical College, Huazhong University of Technology Institutional Review Board with approval given on 25 June 2015 (reference number: TJ-C2015602) (Additional file 1).

In this single-center study, hospitalized patients with primary thyroidectomy in Tongji Hospital will be enrolled. Stochastic indicators were used to generate the random allocation sequence of the patients. Sequentially numbered containers were employed to implement the random allocation sequence and to conceal the sequence until interventions are assigned for implementation. Analysts in our study generated the random allocation sequence while care providers numbered the qualified participants. The surgeon assigned participants to interventions based on the condition of their parathyroid glands during thyroidectomy. All subjects, researchers in the laboratory and data analysts will be blind to the group classification.

Primary endpoint: the ratio of the serum PTH level from the grafted vs. the non-grafted forearm level is no less than 1.5 and the percentages of the 1.5 ratio in the experimental group are obviously higher than those in the control group. Since successful PA was defined as the ratio of the PTH level from the grafted to the non-grafted forearms as not less than 1.5, we set the primary endpoint in line with expert opinion, and the percentages of no less than the 1.5 ratio in the experimental group are obviously higher than those in the control group. 

Secondary endpoints: serum PTH less than 15 pg/ml, and lasting for more than 6 months, as well as a low serum calcium level requiring oral supplements to be taken. Duration of hospital stay will be documented according to hospital charts. During the 1-month to 12-month follow-ups after surgery, patients will be interviewed to assess for postoperative hypocalcemia.

The study was registered at ClinicalTrials.gov and reported according to the Standard Protocol Items: Recommendations for Interventional Trials (SPIRIT) guidelines, including the SPIRIT Figure (Fig. 1) and SPIRIT Checklist (Additional file 2).

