**Fig. 1 Fig1:**
[figure not shown]
Standard Protocol Items: Recommendations for Interventional Trials (SPIRIT) Figure: the schedule of enrollment, interventions, and assessments

The allocation envelope will be opened by the surgeon when conducting the interference. It will not be possible to mask the treatment allocation from the treating surgeon. Nevertheless, measures will be taken to minimize bias:The patients will not be informed regarding whether they will receive the novel site or the traditional site methodTo minimize detection and selection bias, the exact method of PA will not be documented in the medical recordsThe investigator performing the statistical analyses will be blinded to treatment assignments until the final analysis is completed

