### Study participants

Those patients with parathyroid glands that are hard to preserve in situ, or that are mistakenly removed during primary thyroidectomy, will be screened for the inclusion criteria in our study, including malignant and non-malignant disease. Since 10–67% of adults have thyroid nodules on ultrasonography, 10–40% of which were reported as malignant [17, 18], both malignant and non-malignant thyroid diseases were taken into consideration at randomization and analysis. Participants aged from 18 to 65 years old will be enrolled, and those with hyperparathyroidism will be excluded (Fig. 2).

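### One unmasked surgeon opens every envelope of a 1:1 blocked sequence and partly decides entry during surgery, so upcoming allocations could be partly foreseen when patients enter

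*Protocol article*

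**What the plan says.** All references are to the protocol article.

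- **Sequence and operator** (Study design): "A 1:1 block randomization will be performed at the same clinical center and operations will be carried out by the same experienced surgeon".
- **Who learns the allocation** (text after Fig. 1): "The allocation envelope will be opened by the surgeon when conducting the interference", followed by "It will not be possible to mask the treatment allocation from the treating surgeon".
- **Entry** (Study participants): candidates are "Those patients with parathyroid glands that are hard to preserve in situ, or that are mistakenly removed during primary thyroidectomy". Both conditions come to light during the operation.
- **Safeguards** (Study design): "Sequentially numbered containers were employed to implement the random allocation sequence and to conceal the sequence until interventions are assigned for implementation", and "Analysts in our study generated the random allocation sequence while care providers numbered the qualified participants". The text after Fig. 1 adds that patients are not told their site, that the transplantation method is kept out of the medical records, and that the statistician is blinded.
- **Possible stratification** (Study participants): "both malignant and non-malignant thyroid diseases were taken into consideration at randomization and analysis".
- **Recording** (Baseline variables): the attending surgeon completes the case report form (CRF) before surgery, during it and up to 72 h afterwards. Gland number and colour are among the intraoperative items.

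Neither the block size nor whether it varies is stated.

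**The concern.** Each feature is common on its own; the difficulty lies in the combination. A blocked sequence forces the arms level at the end of every block, so past allocations carry information about the next one. Here a single person sees all past allocations, because there is one centre, one operator, and that operator opens the envelopes. The same person's view during surgery of whether a gland can be saved in place helps decide whether a patient enters.

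Concealing the current envelope does not hide what the earlier ones imply. A surgeon who expects a given arm next could, even without intending it, be readier or less ready to enter a patient with a doubtful gland. The condition of the gland plausibly bears on whether the graft functions, which is the primary outcome. The arms could then differ in graft quality, and the planned chi-square comparison would not separate that from the effect of the site.

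**Working it through.** **The plan's own figure.** The only design number nearby is the sample size. With rates of 45% and 65%, two-sided α = 0.05 and power 0.90 (Sample size calculations), the pooled-variance formula gives

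n = [1.960·√(2·0.55·0.45) + 1.2816·√(0.45·0.55 + 0.65·0.35)]² / 0.20² = (1.379 + 0.883)² / 0.04 ≈ 127.9, so 128 per arm.

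This matches the article. The present point does not depend on it and does not change it.

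**Do the stated safeguards stop inference from past allocations?**

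| Safeguard | What it does | Stops the surgeon inferring the next arm? |
|---|---|---|
| Numbered containers | Hide the current allocation | No; earlier ones have been seen |
| List generated by analysts | Separates generation from care | No |
| Care providers number qualified patients | Fixes the order of entry | No; qualifying depends on findings at surgery |
| Method left out of medical records | Limits what others can read | No; the surgeon performed it |
| Patients, laboratory and analysts blinded | Act after entry | No |

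**How predictable is a 1:1 block?** The block size is an assumption, since the article gives none. The calculation also assumes that the size is fixed and that the surgeon knows it or has worked it out.

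In a block of 2m with m places per arm, the remaining allocations are certain once one arm is used up. The expected length of that closing run is 2m/(m+1), so the certain share is [2m/(m+1)] / 2m = 1/(m+1).

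Check for blocks of 4: the six orders AABB, ABAB, ABBA, BAAB, BABA and BBAA have closing runs of 2, 1, 1, 1, 1 and 2. The mean is 8/6 = 1.333, and 1.333/4 = 33.3%.

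The last column is the share of correct guesses when the surgeon always guesses the arm with more places left, from full enumeration of each block.

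| Assumed fixed block | Certain in advance | Of 280 patients | Correct guesses |
|---|---|---|---|
| 2 | 50.0% | 140 | 75.0% |
| 4 | 33.3% | about 93 | 70.8% |
| 6 | 25.0% | 70 | 68.3% |
| 8 | 20.0% | 56 | 66.6% |
| Unblocked | 0% | 0 | 50.0% |

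With randomly varying sizes that the surgeon does not know, fewer allocations are certain. The running imbalance between the arms still gives some information.

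**The case against.** The strongest reply is that predictability depends on a block scheme the article does not give. A condensed article commonly leaves block details to the full protocol, and varying, undisclosed sizes may already be in use. That stands: the missing block size is not the finding, and the table is conditional. It does not remove the point, because varying sizes reduce the information without eliminating it, and nothing described fixes eligibility before the envelope is opened.

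Several stronger readings are tempting but not supported:

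- **That the surgeon keeps the envelopes.** The text says only that the surgeon opens them.
- **That the blocks are small and fixed, or serve no purpose because there are no strata.** Neither size nor type is given. The article says that malignancy was considered at randomisation. If that means stratification, blocking within strata is what makes it work. The Data monitoring section also plans an interim look at each 70 subjects. If that is a total, unblocked arms would range over about 35 ± 1.96·√(70·0.25), or 27 to 43. So dropping blocks altogether is debatable.
- **That the bias can be sized.** If every certain patient in blocks of 4 had graft success shifted 10 points up in one arm and 10 down in the other, the spurious difference would be 1/3 × 20 = 6.7 points. The 10 points have no source in the document. Glands removed by mistake also leave much less room for judgement, so not every predictable place could be steered.
- **That the surgeon picks the arm.** "The surgeon assigned participants to interventions based on the condition of their parathyroid glands during thyroidectomy" can be read that way and sits badly with random allocation. It is a separate matter; the present point holds even if every envelope is followed exactly.

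Gland number and colour are already CRF items, so arm imbalance in gland condition can be examined to some extent. However, the person recording them is the unmasked surgeon, and they need not be recorded before the allocation is known.

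**Conclusion.** The point holds as a design weakness worth correcting. The article itself states the blocks, the single centre, the single unmasked surgeon who opens the envelopes, and an entry criterion that is partly a judgement made at operation. That this judgement is the surgeon's is an inference, though a close one, since the gland is seen during an operation that this surgeon performs.

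For fixed blocks of 2 to 8 whose size is known or inferred, between 50% and 20% of allocations would be certain in advance. Under undisclosed varying sizes the share would be lower, but some predictability would remain. If randomisation is stratified by malignancy, prediction would work within strata whenever the surgeon knows the diagnosis.

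A reader might infer that entry was steered, or that the primary comparison is biased by some known amount. The document supports neither: this is a risk of selection bias whose effect on the result cannot be derived from it.

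**What to change.** 1. **Sequence.** For patients not yet randomised, generate a new list with randomly varying block sizes, within malignancy strata if randomisation is stratified. Withhold the sizes from the surgeon and care team.
2. **Record before opening.** Enter eligibility, the reason for removal, and gland number and colour on the CRF before the envelope is opened, rather than at any time up to 72 h after surgery. This does not prevent prediction, but it fixes the entry decision and the gland findings before the allocation is seen.
3. **Analysis set.** Analyse every patient whose envelope is opened in the allocated arm. This also covers later exits, such as the forearm-visibility criterion under Criteria for discontinuing and quitting the trial, which has no stated timing.
4. **Check.** Compare the recorded gland findings between arms.

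The cost is a regenerated list, one CRF entry made earlier and slightly less exact arm balance. Timing may limit the first step. The Trial status section gives completion in December 2018, which with 12 months of follow-up implies enrolment ending about December 2017, yet it also says recruitment was open at submission. If few patients remain to be randomised, only the recording, the analysis rule and the comparison of gland findings apply.
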